## 1 Introduction

### 1.1 Current state of research

Far-field R-wave sensing (FFS) has been identified as the most common cause for inappropriate mode switch in dual chamber pacemakers.

Under default pacemaker settings and by using a conventional bipolar atrial lead the incidence of inappropriate mode switch is 20%-30%1/2. Applying a far-field R-wave sensing test and adjusting the post ventricular atrial blanking period (PVAB) can reduce the incidence of inappropriate mode switch to 10%3.

In recent studies a newly developed atrial lead with a short bipol distance has shown a relevant reduction on the far-field R-wave amplitude whereas the amplitude of the near field signal (p-wave) remains comparable to conventional leads.

The aim of the study is to show, that using an atrial lead with a very short tip-to-ring spacing can avoid inappropriate mode switch with neither any additional testing nor any individual adjustments of pacemaker settings (Sensing, PVAB)

## 2 Hypothesis given

The new atrial lead Tendril 1699 with a short tip-to-ring distance goes along with a reducing impact on the far-field R-wave amplitude and consequently avoids inappropriate mode switch. Thus by using the new leads with a short bipol spacing there is no need for additional far-field sensing tests and for individual adjustments of pacemaker settings

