## 3 Research Objectives

### 3.1 Primary research objective

The aim is to compare the incidence of inappropriate mode switch (documented as stored IEGMs) between pacemaker systems supplied with a atrial lead with a short bipol spacing (Tendril 1699) and without applying a far-field sensing test or a prolonged PVAB to those with a conventional atrial lead (Tendril 1388, 1688 or 1788) and with an individually optimized PVAB according to the FFS-testing.

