### 7.2 Statistical Methods

Details:

Power = 80%

Groups: 1388/1688/1788 lead vs 1699 lead

Endpoint: % of inappropriate MS due to FFS

When 75 patients are recruited in each group, the lower limit of the observed one-sided 95% confidence interval will be expected to exceed -10% with 80% power when the Standard (1388/1688/1788) proportion, is 5% and the Test (1699) expected proportion, pT, is also 5%; results are based on 1000 simulations using the Newcombe-Wilson score method to construct the confidence interval. (Newcombe RG (1988) Interval estimation for the difference between independent proportions: comparison of eleven methods. Statistics in Medicine 17:873-890.)

Hence, assuming a drop-out rate of 10% you need to recruit **168 patients**.

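### Sections 1.1 and 2 say the 1699 lead avoids inappropriate mode switch, but the only criterion, in 7.2, is non-inferiority within 10 points, which cannot show avoidance or reduction

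*Protocol*

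**What the plan says.** Protocol section 1.1 gives the aim as showing that a lead with very short tip-to-ring spacing "can avoid inappropriate mode switch with neither any additional testing nor any individual adjustments of pacemaker settings". Section 2 has two linked statements. The first is that the new lead "goes along with a reducing impact on the far-field R-wave amplitude and consequently avoids inappropriate mode switch". The second, drawn from the first, is that "there is no need for additional far-field sensing tests and for individual adjustments of pacemaker settings".

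Section 3.1 gives no direction: "The aim is to compare the incidence of inappropriate mode switch (documented as stored IEGMs) between pacemaker systems". The comparator there is a conventional lead "with an individually optimized PVAB according to the FFS-testing".

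Section 7.2 holds the only criterion: "the lower limit of the observed one-sided 95% confidence interval will be expected to exceed -10% with 80% power". It assumes 5% in each arm and 75 patients per arm, and uses the Newcombe-Wilson score method. The protocol does not use the term non-inferiority, does not define the direction of the difference, and describes no test against zero.

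**The concern.** A hypothesis of avoidance and a criterion that tolerates an excess of up to 10 points are different statements. If the trial meets 7.2, the report can present the section 2 hypothesis as confirmed even though the new-lead arm had more events than control. If instead the lead has clearly fewer events, the protocol fixes no rule under which a reduction could be claimed, and a rule chosen after the data are seen would carry less weight. What is at stake is the conclusion that the trial may draw. The sample size and the primary test are not in question.

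**Working it through.** **Inputs.** From section 7.2: n = 75 per arm, margin 10 points, one-sided 95% limit (z = 1.645), Newcombe-Wilson method, 5% in both arms. From section 1.1: 10% incidence after far-field testing and PVAB adjustment. New-lead rates other than 5% are assumptions, shown as a range.

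**Formula.** Let S and T be the observed proportions for Standard and Test. The event is unfavourable, so a limit of -10% makes sense only for S - T. With l_S the lower Wilson limit for S and u_T the upper Wilson limit for T:

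L = (S - T) - sqrt[(S - l_S)² + (u_T - T)²]

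Section 7.2 is met if L > -0.10. Probabilities come from summing the two binomial distributions over all pairs of counts that satisfy the condition.

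**Reproducing the plan.** At 5% and 5% with 75 per arm, the probability that L > -0.10 is 80.6%, against the stated 80%. For dropout, 75/0.9 = 83.3, rounded up to 84 per arm, or 168 in total as stated. So 7.2 is a one-sided 5% non-inferiority test with a 10-point margin.

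**What meeting 7.2 allows.** Take 7 control and 8 new-lead events:
- S = 7/75 = 0.0933 and l_S = 0.0514
- T = 8/75 = 0.1067 and u_T = 0.1796
- L = -0.0133 - sqrt(0.0419² + 0.0729²) = -0.0133 - 0.0841 = -0.0974, which exceeds -0.10

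The criterion is also met at 4 against 5 and at 0 against 3.

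| True rates (control, new lead) | Probability of meeting 7.2 |
|---|---|
| 5%, 5% | 80.6% |
| 5%, 10% | 28% |
| 5%, 12% | 15% |
| 5%, 15% (at the margin) | 4.7% |

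At 5% and 5%, the probability of meeting 7.2 with more events in the new-lead arm than in control is 23%.

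**Reading the same limit against 0.** L exceeds 0 at 4 against 0 events (L = 0.008), 6 against 1 (0.008), 7 against 2 (0.001) and 10 against 4 (0.0004).

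| Control rate | Assumed new-lead rate | Probability that L > 0 |
|---|---|---|
| 5% (section 7.2) | 2% | 19% |
| 5% | 1% | 32% |
| 5% | 0% | 52% |
| 10% (section 1.1) | 5% | 32% |
| 10% | 2% | 68% |
| 10% | 1% | 82% |
| 10% | 0% | 95% |

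At equal true rates from 1% to 20%, the probability that L > 0 is 0.3% to 5.1%, so the error of this step stays at about the nominal 5%. Any result with L > 0 also has L > -0.10, so the second step is reached only through the first.

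**The case against.** The strongest reply is that the operative claim is the second sentence of section 2: testing and individual adjustment are not needed. Only the control arm receives both, so non-inferiority to that arm is the natural test. This stands. A reader might infer that the whole hypothesis is untested, or that the protocol promises superiority over the optimised control. The documents support neither. No section claims superiority over that control, and equal counts such as 8 against 8, which also meet 7.2, fit the second half of the hypothesis.

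It can also be said that *avoids* has no stated comparator and may refer to the 20%-30% under default settings in section 1.1. That reading is possible, but no arm receives a conventional lead at default settings, so the trial could not test it either.

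A follow-on superiority reading is often left to the statistical analysis plan, which may exist. Its absence from the protocol is therefore no error in itself, and a non-inferiority trial without one is legitimate. An analysis plan would not, however, change a protocol hypothesis worded differently from the protocol's criterion.

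Finally, superiority would support *reduces* and not *avoids*: at 10 against 4 events the limit exceeds 0 while the new-lead arm still has 4/75 = 5.3%. This also stands, and the fix below respects it.

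**Conclusion.** The concern holds in a limited form. The criterion in 7.2 suits the claim that additional testing is unnecessary, within the 10-point margin. It does not test the claim of avoidance in sections 1.1 and 2. A positive result is compatible with more events on the new lead: 7 against 8 meets it, as does a trial with true rates of 5% and 10% in 28% of cases. These figures rest on 75 evaluable patients per arm, independent binomial counts, and the difference taken as Standard minus Test, the reading that reproduces the stated power. The gain from a second step depends on rates the protocol does not settle. It is small to moderate at the 5% control rate of 7.2, and larger at the 10% of section 1.1 only if the new-lead rate is well below 5%.

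**What to change.** 1. In section 2, and consistently in 1.1 and 3.1, state the hypothesis that 7.2 tests: incidence with the 1699 lead and the protocol's fixed 60 ms PVAB is less than 10 percentage points above that of the FFS-optimised control, with the difference defined as Standard minus Test. Limit the conclusion of a positive trial to that statement.
2. In 7.2, pre-specify that if non-inferiority is met, the same one-sided 95% Newcombe-Wilson limit is read against 0. Claim that the new lead reduces inappropriate mode switch compared with the optimised control only if the limit exceeds 0, and do not word that result as avoidance. Say that this step does not drive the sample size.

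The cost is a few sentences, a more modest hypothesis, and one further reading of an interval that is computed anyway. No patients or data are added, and because the steps are in fixed order there is essentially no extra type I error.

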## 3 Research Objectives

### 3.1 Primary research objective

The aim is to compare the incidence of inappropriate mode switch (documented as stored IEGMs) between pacemaker systems supplied with a atrial lead with a short bipol spacing (Tendril 1699) and without applying a far-field sensing test or a prolonged PVAB to those with a conventional atrial lead (Tendril 1388, 1688 or 1788) and with an individually optimized PVAB according to the FFS-testing.

### 3.2 Secondary research objective

- Influence of the atrial lead position and the ventricular pacing percentage on the

occurrence of inappropriate mode switch

- Detection of atrial flutter in the pacemaker storage
- Occurrence of 2:1-Lock-in of atrial flutter

### 4.3 Acceptance as study centre

Prior to initiation of the Avoid FFS trial study centres have to provide the sponsor with the following documents:

- Signed "Investigator Agreement"
- CV (up to date) of the investigators und Co-Investigators
- Written and signed approval of the Ethic Committee

### 4.4 Responsibilities and duties

#### 4.5.1 Investigator und Co-Investigator

In the course of the Avoid FFS trial investigators and co-investigators have the following responsibilities and duties:

- Applying for ethical review of the study protocol by the Ethic Committee
- Providing information to the Ethic Committee in case of protocol amendments
- Providing information to and educating patients before recruiting
- Recruiting of patients meeting all of the inclusion criteria and none of the exclusion criteria
- Performing the planned examinations and doing the follow ups in line with the Avoid FFS protocol, filling in the requested forms or transferring the data via electronic storage media
- Reporting adverse events to the sponsors within one working day after occurrence
- Reporting serious adverse events additionally to the Ethic Committee and the public authorities without delay

#### 4.5.2 Principle Investigator

- In addition to the above mentioned tasks the principle Investigator (PI) has to evaluate in case of serious adverse events if continuing the study goes along without negative influence on safety and well-being of each participant or the total study population
- In case of potential harm the principle investigator will discontinue the Avoid FFS trial ahead of time.
- Approving the study protocol before trial start or after protocol amendments

#### Sponsor

- Selecting and activating new study centres after receipt of the required documents
- Monitoring
- Creating, analysing and maintaining a database
- Transferring paper-based data in the database
- Approving the study protocol prior to study start and after protocol amendments respectively

### 4.6 Data processing and data privacy

All collected and on forms documented data will be stored in anonymized form in electronic files and processed according to the current data privacy regulations and legal framework.

The database will be created and maintained by the sponsor of the Avoid FFS trial, the St. Jude Medical GmbH – Eschborn. After study completion and publication the centres and the sponsor have access to the data pool.

### 4.7 Monitoring Agreements

The run of the trial will be assisted by employees of St. Jude Medical GmbH with visits on-site and counselling hotline.

In terms of monitoring the following agreements are made:

On the condition of adequate supervision and under the guarantee of confidentiality the investigator will give the site managers (monitors) access to all stored follow-up data, the relevant sections of the anonymised patient´s file or the pacemaker settings and pacemaker derived data.

This Monitoring serves as a quality control and ensures the data accuracy in the Avoid FFS data base. In case of study related questions or technical issues the investigator is free to contact the Avoid FFS study managers or other employees of St. Jude Medical GmbH in accordance with usual practice.

### 4.8 Publishing control

After completing the trial a report will be compiled.

The Investigator agrees on publishing the collected data and gained findings along with St. Jude Medical. The collected study data can be utilized for giving talks at a congress or for medical publishing based on a mutually agreement among the parties.

The first publication of the study results can be done under the principle investigator´s authorship, if he has included an adequate number of participants.

After completing the trial and finishing the final report the study centres as well as St. Jude Medical will have access to the complete data pool

### 4.9 Modification of the study protocol

During the ongoing study new scientific findings, interim results and adverse events can require amendments. If it is necessary or reasonable to expand, modify or eliminate areas of interest and investigations, as detailed in the current study protocol, the relevant protocol sections will be revised and attached to all delivered study protocols after written approval by the principle investigator and the sponsor.

The investigators are in charge to report all amendments of the protocol to each of the responsible ethics committees.

### 4.10 Planned duration of study

The study is designed to include about 170 patients.

The recruiting period will last roughly 12 months.

With an expected start in October 2006 and a follow up period of a minimum of 3 months the study will end in the middle of 2008.

## 5 Methodology

The trial is designed as prospective, randomised, multicentric and multinational study

### 5.1 Study course

After giving a written informed consent for participating in the trial the patient will receive a dual chamber pacemaker according to the study protocol.

Prior to pacemaker implantation the patient will be randomly assigned to the study group with receiving a novel atrial lead with a short tip-to-ring distance (Tendril 1699) or to the control group with receiving a conventional atrial lead (Tendril 1388, 1688 or 1788)

In the study group the PVAB will be fixedly programmed at 60ms. Whereas in the control group the coupling interval will be defined according to a far-field sensing test and finally the optimized PVAB will be programmed at the coupling interval plus 25 ms. (see below: 5.4.5 far-field sensing test, as well as 5.5 pacemaker programming guidelines)

The primary endpoint will be the occurrence of an inappropriate mode switch due to FFS assessed by stored episodes of the pacemaker within the first 3 months after implantation.

In case of an inappropriate mode switch the far-field sensing test will also be applied to a patient of the study and the PVAB will be programmed at the coupling interval plus 25ms. The 3 months follow up of these patients will be continued.

### 5.2 Study population

In order to participate in the AVOID FFS trial, all of the following inclusion criteria must be met and all exclusion criteria must not be met. Patients with a pacemaker exchange are not eligible for the study.

#### 5.2.1 Inclusion criteria

- Indication for a dual chamber pacing system (according to national and international

guidelines)

- Implantation of a St. Jude Medical pacemaker: Identity (ADx) DR, Victory DR or models released later on with same functionality.
- Age ≥ 18 years

#### 5.2.2 Exclusion criteria

- Persistent or permanent atrial tachyarrhythmias
- Pacemaker exchange
- Pregnancy
- Participation in another trial investigating an implantable medical device
- No availability for follow-up visits
- Absence of the patient´s written informed consent form
- History of cardiac surgery or myocardial infarction within 4 weeks prior to enrolment
- Planned cardiac surgery within the next 3 months after randomisation

### 5.3 Informed consent

All patients will be informed about background, objectives and risks of the study by the treating physician and will be given the opportunity to discuss all their questions concerning the study.

Only patients who gave written informed consent will be eligible to participate in the trial.

The used informed consent form for the pacemaker implantation and the additional information and consent form for the study are enclosed for review by the ethics board.

The study information and consent form informs the patient additionally about additional, study-related procedures and about anonymized data handling and electronically data processing due to the study.

### 5.4 Data collection and documentation

The study centre receives an Avoid FFS study ring binder and one or several patient folder(s), in which all forms and records for each patient are stored in order to document the study data as well as the informed consent

#### 5.4.1 Patient enrolment

By including a patient an „enrolment form“ with all data will be filled in and a completed copy with a signed patient informed consent form will be archived in the patient´s file.

The following data will be recorded:

- Patient informed consent form
- Anonymized patient identification
  - initials
  - gender
  - date of birth
- Antiarrhythmic medication
- Underlying cardiac disease
- Underlying bradycardia and its symptoms
- Randomisation

#### 5.4.2 Implantation and revision surgery

The patients will receive a licensed pacemaker (Identity ADX DR, XL DR, Victory DR or any dual chamber follow-up model produced by St Jude Medical) and according to randomisation a matching, bipol, CE-certified atrial lead (Tendril 1699 in the study group and Tendril 1388, 1688 or 1788 in the control group), as well as a CE-certified ventricular lead (see section 6).

An implantation form will be filled in for each operation. Even in case of revision surgery without device removal or change an implantation form will document the reasoning for revision.

The following implantation data will be recorded:

- Implantation date
- Device-type, device-id and serial number
- Atrial and ventricular sensing threshold (PSA / pacemaker)
- Atrial and ventricular pacing threshold and lead impedance (PSA / pacemaker)
- Atrial and ventricular signal amplitude (PSA / pacemaker)
- Atrial lead placement
- Adverse events / surgery related events

#### 5.4.3 Follow-Up

Each follow-up visit will be documented by filling in a „follow up“-form. There will be a documentation of even unscheduled pacemaker testing due to arrhythmia, treatments or hospital stays.

For each participant a PHD (Pre Hospital Discharge)-testing of the pacemaker system, as well as follow-up visit in 1 and 3 month(s) after implantation are scheduled.

- **PHD:** prior to hospital Discharge
- **F1-F2:** 1 month und 3 months  14 days after primary implantation

##### 5.4.3.1 Follow-up visit und documentation

Following tests will be done and following parameter will be recorded at each follow-up visit:

**PHD**

- Follow-up date
- Current antiarrhythmic medication
- Pacemaker parameters (sensing and pacing thresholds, impedance of the leads etc)
- Keeping records of AF-burden-, mode-switch-, frequency- and sensor histogram, inclusive all stored IEGMs, and deleting the pacemaker storage afterwards
- Far-field sensing test within the control group only (please see 5.4.5)
- Programming according to the study guidelines (please see 5.5)
- Adverse events

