**F1 (1 month after implantation ± 14 days)**

- Follow-up date
- Current antiarrhythmic medication
- Pacemaker parameters (sensing and pacing thresholds, impedance of the leads etc)
- Keeping records of AF-burden-, mode-switch-, frequency- and sensor histogram, inclusive all stored IEGMs, and deleting the pacemaker storage afterwards
- Analysing of the mode-switch IEGMs in terms of inappropriate mode-switch episodes. In case of inappropriate mode-switch episodes a participant has reached the primary endpoint. The patient will undergo an individual optimisation of the PVAB according to the far-field sensing test results and stay in the study group until the end of the trial
- Programming of the pacemaker according to the study guidelines
- Any hospital stays since discharge, reason for hospitalisation
- Adverse events

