#### 5.4.5 Far-field Sensing Test

Only patients within the control group and those of the study group with inappropriate mode switch episodes (stored in the IEGM memory) will undergo a far-field sensing test..

- Hereby intraatrial and intraventricular IEGM (atrial sensing amplification, Vtip-Vring), as well as extended marker and external ECG recordings of the pacemaker programmer are used
- Temporary programmed parametric settings
- Atrial sensing: 0.1 mV, bipolar
- PVAB 60 ms
- AV-time 70ms (ventricular pacing)

An ECG-stripe, recorded with 50 mm/s, has to be printed out. If there are black boxes (representing p-wave sensing within in the refractory period) the interval from the ventricular pacing marker to the P-marker (black box) has to be measured. This interval equals the coupling interval (CI) of the far-field R-wave signal.

The optimised PVAB will be programmed at CI +25ms, but not less than 85 ms.

The testing will be recorded with intrinsic conduction but also under pacing condition. In the course of the study a prolongation of the PVAB according to FFS test results is allowed. But there will be no shortening of the PVAB, only due to relevant clinical reasons.

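### The pre-discharge list deletes device storage before the control-only far-field test, so an episode provoked by the test could later count as a control-arm endpoint

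*Protocol*

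**What the plan says.** Protocol 5.1 defines the primary endpoint as an inappropriate mode switch due to far-field sensing, taken from the pacemaker's stored episodes in the first 3 months after implantation.

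The PHD list in 5.4.3.1 first has the storage step: "Keeping records of AF-burden-, mode-switch-, frequency- and sensor histogram, inclusive all stored IEGMs, and deleting the pacemaker storage afterwards". The entry directly below it, which applies to one arm, reads "Far-field sensing test within the control group only (please see 5.4.5"). The entry after that is the setting of the device under section 5.5. No deletion is listed after the test.

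Section 5.4.5 gives the temporary test settings: "Atrial sensing: 0.1 mV, bipolar", a PVAB of 60 ms and an AV time of 70 ms, which produces ventricular pacing. For comparison, the atrial sensing setting in 5.5 is 0.3 mV, and 5.4.5 sets the optimised control PVAB at no less than 85 ms.

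At F1 the stored mode-switch electrograms are analysed: "In case of inappropriate mode-switch episodes a participant has reached the primary endpoint". Neither 5.1 nor the F1 list sets aside episodes recorded while the device was being tested.

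Section 7.2 frames the comparison as non-inferiority: "the lower limit of the observed one-sided 95% confidence interval will be expected to exceed -10% with 80% power", with both rates at 5% and 75 patients per group.

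**The concern.** The far-field test is designed to make the ventricular signal visible in the atrial channel, and that signal is the cause of the events the trial counts. If a site follows the PHD list from top to bottom, the memory is empty when the test begins and is next read at F1. A mode switch stored during the test would then look like a spontaneous event from the first month.

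Study-arm patients have no far-field test at PHD, so any such artefact is confined to the control arm. A falsely high control rate in a non-inferiority comparison makes the new lead look better than it is. Starting the endpoint count at the PHD clearing would not help, because the test comes after that clearing.

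**Working it through.** **Inputs**
- From 7.2: 75 per group, 5% in each arm, one-sided 95% Newcombe-Wilson interval, limit of -10 points (read as Standard minus Test), 80% power, 10% drop-out.
- Assumed, because the documents give no value: c, the share of otherwise event-free controls who carry a test-provoked stored episode. The values used run from 0 to 4%.

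**Formula.** Let pT and pS be the observed study and control proportions, uT the Wilson upper limit for the study arm and lS the Wilson lower limit for the control arm, each at one-sided 5%. The upper limit for study minus control is

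U = (pT - pS) + sqrt[(uT - pT)² + (pS - lS)²].

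Non-inferiority is claimed if U < 0.10. This is the same as the lower limit for Standard minus Test exceeding -10%.

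**Step 1: the plan's own figures.** Exact binomial enumeration over all outcomes at 5%/5% with 75 per arm gives P(U < 0.10) = 0.806, against the stated 80%. At one-sided 2.5% it would be 0.718, so the one-sided 5% reading is the plan's. For drop-out, 75/0.9 = 83.3, rounded up to 84 per arm, and 2 × 84 = 168, as stated.

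**Step 2: weight of single events.** One false control event adds 1/75 = 1.3 points to the control rate. Take 7 study events as an example: pT = 0.0933, uT = 0.1636.
- 4 control events: pS = 0.0533, lS = 0.0242. U = 0.0400 + sqrt(0.0703² + 0.0291²) = 0.116. Not shown.
- 6 control events: pS = 0.0800, lS = 0.0419. U = 0.0133 + sqrt(0.0703² + 0.0381²) = 0.093. Claimed.

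Two false control events reverse the conclusion here. The example was chosen close to the margin, so it shows that a reversal is possible, not that it is likely.

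**Step 3: false-claim rate at the margin.** True rates are 5% control and 15% study, 75 per arm. The recorded control rate becomes 0.05 + 0.95c.

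| c | Recorded control rate | P(non-inferiority claimed) |
| --- | --- | --- |
| 0 | 5.00% | 4.7% |
| 1% | 5.95% | 6.9% |
| 2% | 6.90% | 9.8% |
| 4% | 8.80% | 17.3% |

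In expected counts, c = 2% is 75 × 0.95 × 0.02 = 1.4 patients, and c = 4% is 2.9 patients.

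**The case against.** A reader might infer that the memory is always cleared before the test and that test-provoked episodes will be counted as control endpoints. The protocol does not support that, for four reasons.

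1. **The order is not stated to be binding.** The sentence that opens 5.4.3.1 says what is done and recorded at each visit, not in what sequence. The deletion bullet ties deletion to the saving of records, so a site that tests, programmes and then clears also complies. This stands. It does not close the gap, because each site is then free to clear before or after the test.
2. **Recording during the test is not established.** Read as a strict sequence, the same list puts the section 5.5 programming, where mode switch and its recording trigger are set, after the test. Section 5.4.5 describes a printed strip and measured intervals and mentions no mode switch. The test must also run long enough to meet the detection criterion. This is the main uncertainty. Against it, the temporary settings do not turn mode switching or storage off, and the PHD visit collects mode-switch histograms and stored electrograms, so the device may already be recording.
3. **Episodes are read, not counted automatically.** The PHD date is recorded, and a reader might recognise a test-session episode. Detailed reading rules may sit in an analysis plan or reading manual that is not shown, and their absence from the protocol is not itself a fault. Still, the protocol as written does not require such episodes to be set aside.
4. **The contamination rates are illustrative.** They have no source in the documents, and zero is a possible value.

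The mechanism also does not extend to F1 and F2. The far-field test is listed there for patients who have already reached the endpoint, and F2 is the end of the trial.

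**Conclusion.** The point holds in conditional form. The listed order places deletion before a control-only test whose settings favour the sensing that the endpoint counts. No later clearing is listed, and neither the endpoint definition nor the F1 list excludes test-session episodes. If mode switching and electrogram storage run during the test, false endpoints could enter the control arm only and would favour Tendril 1699.

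How often this would happen cannot be derived from the documents. The rise in the false-claim rate from 4.7% to 6.9%, 9.8% or 17.3% is a sensitivity range that rests on the assumed shares of 1%, 2% and 4%, not an estimate. The planned sample size and power are unaffected and reproduce. Because the risk runs in one direction, touches the primary endpoint and costs almost nothing to remove, it should be closed.

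**What to change.** In the PHD list of 5.4.3.1, state the order explicitly: save the histograms and stored electrograms first; then carry out the far-field test (control group) and the final programming; then delete the storage as the last step of the visit.

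Add one sentence to 5.1: episodes time-stamped within a device-test session do not count as primary endpoints.

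The F1 and F2 lists need no reordering. The cost is a moved bullet and one sentence. No patient, test or visit is added, and 75 per group and 168 in total stay as they are.
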